## Interventions

There are five pairs of interventions being tested in this trial; however, each participating hospital will only take part in three of these five possible comparisons. The non-allocated comparisons and all other aspects of the caesarean section will be performed at the discretion of the surgeon. For example, for women randomised in a hospital which is taking part in the three comparisons: sharp vs blunt abdominal entry; double vs single layer uterine closure; and closure vs non-closure of the peritoneum; then it will be at the discretion of the surgeon as to whether there is exteriorisation of the uterus or not, and what suture material is used for uterine repair.

All allocated techniques should be performed unless there are overwhelming reasons not to do so. For example, at the time of surgery it may become apparent that there is no clear peritoneal layer overlying the uterus in a woman undergoing a second caesarean section. In these circumstances, it will not be possible to close this peritoneal layer during the repair. Other clinical circumstances may also change during the course of the surgical procedure after a particular intervention has been allocated. If the clinician performing the caesarean section is certain that a non-allocated intervention is necessary then this should be performed and the reasons for not complying with the allocated intervention recorded on the data collection form.

### 1. Blunt versus sharp abdominal entry

#### Sharp abdominal entry

The abdomen is entered using a scalpel to divide the abdominal skin. Each subsequent layer of the abdomen (fat, rectus sheath and parietal peritoneum) is then separately identified and divided using either a scalpel or scissors.

#### Blunt abdominal entry

The abdomen is entered using a scalpel to divide the abdominal skin. The scalpel is then used to divide the fat and rectus sheath in the midline and the rectus sheath incision is extended manually (without the use of a scalpel or scissors). The parietal peritoneum is then entered digitally and the defect enlarged manually.

For some women with a previous caesarean section, blunt abdominal entry may be impeded by scar tissue. If this is the case, surgeons should use whatever technique is necessary to effect abdominal entry with the minimum of risk to the well being of the woman. If during the blunt abdominal entry a scalpel or scissors are used to extend the original incision in the sheath or peritoneum, then this should be recorded as a sharp abdominal entry on the Data Collection Booklet.

### 2. Exteriorisation of uterus for repair versus intra-abdominal repair

#### Exteriorisation

Once the placenta has been delivered the uterus is drawn from the pelvis to rest on the anterior abdominal wall so that the uterine incision can clearly be visualised. The uterus is then repaired (with or without repair of the pelvic peritoneum) and the uterus is then returned to the pelvis.

If exteriorisation of the uterus is not possible because of pain, then intra-abdominal repair may be necessary. This should be recorded as intra-abdominal repair on the Data Collection Booklet and the reason for non-compliance with the allocated intervention given as "intra-operative pain".

#### Intra-abdominal repair

The uterine incision is repaired while in the pelvis.

### 3. Single versus double layer closure of the uterus

#### Double layer uterine closure

The uterine incision is closed with two layers of sutures. Each layer may be continuous, continuous locking, interrupted or any other accepted technique.

The first layer opposes the endometrial aspect of the uterine muscle layer and the second layer of sutures bring together the serosal layer ensuring haemostasis and complete apposition of the incision.

#### Single layer uterine closure

This technique involves bringing both edges of the uterine incision together with a single layer of sutures. This may be a continuous, continuous locking or an interrupted layer of sutures.

Haemostasis of the incision can be effected by using additional single or 'figure of eight' sutures as judged necessary by the surgeon regardless of the method of closure undertaken.

### 4. Closure or non-closure of the peritoneum

#### Closure of the peritoneum

Women allocated closure of the peritoneum should have the pelvic and parietal peritoneum closed. The techniques of closure, including the suture material used, will be at the discretion of the clinician.

In some women with a previous caesarean section, repair of the pelvic peritoneum, the parietal peritoneum or both may be impossible. If this is the case, surgeons should record this as non-closure of the peritoneum on the Data Collection Booklet including the reason for non-compliance.

#### Non-closure of the peritoneum

In women allocated non-closure, the peritoneum should not be closed.

For either closure or non-closure of the peritoneum, haemostasis should be affected as usual including, where necessary, the use of haemostatic sutures.

### 5. Chromic catgut versus Polyglactin-910 for uterine repair

#### Chromic catgut

The uterus will be repaired using No. 1 chromic catgut. This may be a continuous, continuous locking or an interrupted layer of sutures.

#### Polyglactin-910

The uterus will be repaired using No. 1 Polyglactin-910. This may be a continuous, continuous locking or an interrupted layer of sutures.

Haemostasis of the incision can be effected by using additional single or 'figure of eight' sutures as judged necessary by the surgeon.

Regardless of the type of suture material allocated, any unused sutures **should not **be used to effect repair of any other tissue layer. The standard materials used in each centre should be used to close the peritoneum (if performed), the sheath, the subcutaneous tissue (if closed) and the skin.

Use of the allocated suture material to close other tissue layers will render the randomised comparison of Polyglactin-910 versus chromic catgut invalid (particularly if there is differential use, i.e. the Polyglactin-910 is used and the chromic catgut is not used to close the sheath).

## Other aspects of clinical management

All other aspects of the operation, apart from those randomly allocated, will be determined by the attending surgeon and anaesthetist including the choice of suture materials and the techniques for repair used.

Women participating in the trial will be managed in whatever way seems best for them. Participation in the trial does not restrict the use of any other therapeutic or diagnostic procedures judged necessary by the attending clinician. This applies particularly to the use of analgesia, perioperative antibiotics or thromboprophylaxis. Current hospital practice should be continued, regardless of participation in the trial.

It is essential that the other aspects of the caesarean section operation remain constant regardless of those aspects which are allocated. So, for example, if it is the usual practice of the surgeon to infiltrate the skin edges with local anaesthetic for post-operative analgesia, this should continue for all women operated on by that surgeon regardless of whether the women is allocated sharp or blunt abdominal entry. The use of other interventions, such as per-rectum analgesia, should similarly be the same for women in each allocated group. Differential use of these co-interventions between randomised groups will render the comparisons of the trial invalid.

## Training in surgical techniques

Of the techniques being compared, training may be required in single or double layer uterine closure and in blunt and sharp abdominal entry. All the other techniques are familiar to all obstetricians in clinical practice in the participating centres.

Each participating centre will initiate, maintain and document a training programme which ensures that all personnel involved in the undertaking of caesarean sections are familiar with the techniques being compared before they enter women into the trial. Training will vary between countries according to the national standards of training in new surgical techniques employed by each participating country. For example, if the accepted standard for surgical training in a country is that operators must perform a certain number of procedures before they are judged to be competent in that procedure, then this process should be followed. If, however, the national standard is that operators are judged to be competent when a senior surgeon judges them to be competent, then this process should be followed. The accepted standard of surgical training in each centre will be determined at the start of the trial and specific documentation will be produced for each country to facilitate the recording of details of each operator 'accredited' to operate on women recruited to the trial. To facilitate training a film of all the interventions being tested in CORONIS will be provided to participating centres. In individual countries, visits by the Regional Co-ordinator to participating hospitals to teach specific surgical techniques may be required so that experience in the participating hospitals can be disseminated rapidly.

Each participating centre will appoint a senior obstetrician to ensure that only clinical staff competent in the various surgical techniques to be used in the trial are 'authorised' to operate. A list of these personnel will be kept by the local centre with a copy being kept by each Regional Trial Office.

## Trial eligibility

Women **ARE **eligible for trial entry if:

• They are undergoing delivery by lower segment Caesarean section through a transverse abdominal incision, *irrespective of fever in labour, gestational age or whether they have a multiple pregnancy*.

Women are **NOT **eligible if :

• There is a clear indication for a particular surgical technique or material to be used that prevents any of the allocated interventions being used,

*e.g. for a woman with a previous vertical abdominal incision it maybe considered inappropriate to do a transverse abdominal incision for this caesarean section. However, if a transverse incision is going to be performed the woman is eligible*.

• They have had more than one previous caesarean section.

• They have already been recruited into the trial during a previous pregnancy.

## Trial entry and consent

Each participating country and hospital, with advice from their research ethics committee, will decide how best to provide information to women about the trial and seek informed consent.

Information leaflets will be made available to local centres, in appropriate languages, which explain the justification for the trial, the process of trial entry and follow up. Once a woman becomes eligible, the trial should be discussed with her (and her partner as appropriate).

During this discussion the following points should be addressed:

• that consent is being sought for the woman's participation in a randomised controlled trial;

• the trial will compare different aspects of the caesarean section techniques, all of which are in common practice throughout the world;

• that the aspects being compared will be allocated at random;

• that participation in the trial is voluntary and declining to enter the trial will not affect the quality of the medical care the woman receives;

• that one hospital visit or home visit is required at six weeks after the birth of her baby;

• that she is free to withdraw her consent to participate in the trial at any time.

All women will be required to sign a formal consent form if they agree to participate in the trial. If women are not able to sign a consent form, the method of recording consent which is currently used in that setting will be used for the trial (for example, the recording of a thumb print from the woman on the consent form). If there is no objection to trial entry, a few brief details will then be recorded on the trial data collection form.

This information is collected for three reasons:

i. to check eligibility,

ii. to enable later (unbiased) description of the women studied,

iii. to assist follow-up.

## Measurement of outcomes

### Primary outcome

1. Death or maternal infectious morbidity (one or more of the following: antibiotic use for maternal febrile morbidity during postnatal hospital stay, antibiotic use for endometritis, wound infection or peritonitis) or further operative procedures; or blood transfusion.

*Note: although there are concerns about the use of composite outcomes, we believe that the advantage of increased precision of the estimate of short term morbidity out-weighs any potential disadvantages. All the outcomes included in this composite are associated with the primary objective of the trial and are likely to act in the same direction as each other thereby preventing any dilution of the treatment effect*.

### Secondary outcomes – all within 6 weeks of delivery unless stated otherwise

#### Clinical

1. Death.

2. Febrile morbidity.

*Note: any clinical diagnosis of fever >38°C made by a health professional and treated with antibiotics during postnatal hospital stay*.

3. Endometritis.

*Note: any clinical diagnosis of endometritis made by a health professional and treated with antibiotics during the first six weeks after the caesarean section. For events which occur after discharge from hospital this information will be gathered by interview with each woman six weeks after the caesarean section*.

4. Wound infection treated with antibiotics.

*Note: any antibiotics prescribed specifically for a wound infection. This information will be gathered by interview with each woman at six weeks after the caesarean section*.

5. Operative procedures on wound.

*Note: this will include any procedures on the wound because of infection, dehiscence or haematoma within the first six weeks following delivery*.

6. Pain.

*Note: this will be a subjective assessment of post-operative pain by the women at the time of hospital discharge and at six weeks. In addition a category of 'severe pain' will be recorded if the woman is prescribed additional analgesia over and above routine 24–48 hours after surgery*.

7. Blood transfusion.

8. Interventions used for severe primary post-partum haemorrhage (PPH).

*Note: this is defined as women who (a) require additonal uterotonics over and above routine, (b) where a brace suture is used (eg. B-Lynch suture), (c) where internal iliac artery, or other major artery, ligation is performed, (d) where balloon tamponade or uterine packing is performed or (e) where a hysterectomy is performed*.

9. Stillbirth after trial entry.

*Note: it is possible that a delay in abdominal entry associated with different methods may adversely affect neonatal outcome*.

10. Apgar score < 3 at five minutes.

11. Laceration of baby at time of caesarean section.

12. Death of the baby by six weeks of age.

13. Other severe maternal morbidity.

*Note: this will include events such as peritonitis, severe secondary post-partum haemorrhage, deep venous thromboses, pulmonary embolism, and sepsis within six weeks of delivery, etc*.

#### Health Service Utilisation

14. Duration of operation (from incision to closure).

15. Duration of hospital stay post-caesarean section.

16. Duration of stay in Intensive Care Unit post-caesarean section.

17. Number and duration of re-admissions to hospital within 6 weeks of the caesarean section.

## Data collection

Information will be collected at the following times:

• at trial entry;

• immediately following the operation;

• at discharge from hospital (including transfer to another hospital);

• at six weeks after delivery.

Information at trial entry including eligibility and maternal characteristics will be collected from the hospital notes onto the trial data collection booklet. Once the caesarean section is complete information about the procedure will be recorded by the surgeon who performed the operation. At discharge from hospital (or transfer to another hospital) staff on the postnatal ward will record information about the trial outcomes from hospital records.

In addition, all women will be seen at six weeks postpartum to determine whether they have experienced any of the other trial outcomes. Follow-up will be achieved in a variety of ways: women will be encouraged to return to the hospital at six weeks postpartum for a routine check-up at which point trial specific information can also be requested. Women who do not return at six weeks will be sought and interviewed by appropriately trained personnel employed by the trial either by telephone (if feasible) or by home visits.

To facilitate the accurate recording of clinical diagnoses and treatments after hospital discharge women will be provided with a medical card at discharge from hospital. Women will ask health professionals who they see after hospital discharge to record any diagnoses made and record the treatment prescribed. Although this is unlikely to be used on all occasions, it should enhance the quality of the information obtained at the six week interview.

Sufficient descriptive information will be collected about the participating women in the trial to allow further follow-up if funds can be secured in the future. Of particular interest in the future is the effect that operative techniques may have on future pregnancies, specifically problems with conception, antenatal complications such as the incidence of abruption, mode of delivery especially 'in-labour' caesarean sections, placental problems, subsequent wound complications and stillbirths.

## Analysis

The analysis of this trial will be by 'intention-to-treat'. Therefore women will be analysed by the groups into which they were randomised regardless of what interventions they received.

For the analysis, the risk ratio for each outcome will be estimated for each of the five surgical techniques. A 95% confidence interval will be used for the main outcome although any results which are of "borderline" statistical significance will be treated cautiously owing to the five comparisons being made. For secondary outcomes, 99% confidence intervals will be calculated in order to take account of the number of secondary outcomes.

The focus of the analysis will be on the main effects of the five interventions. However, pairwise interactions between any two interventions will be tested for and the results will be stratified accordingly if interactions are found. Alternatively, if risk differences provide a better fit to the data than risk ratios, then these will be presented instead. It is recognised that the study has low power to detect interactions, therefore, an interaction test which is not statistically significant does not mean that there really is no interaction. Alternatively, there are 24 possible interaction pairs which can be tested for, so "significant interactions" may arise by chance. Hence, the interaction results will be interpreted cautiously together with other evidence such as biological plausibility and consistency (e.g. across countries).

In addition, pre-defined subgroup analysis will be performed based on outcomes stratified by:

i. 'In-labour' or not 'in-labour' caesarean section,

ii. Single and multiple pregnancy,

iii. HIV positivity (positive, negative, not known),

iv. Number of previous caesarean sections (none or one),

v. Presence of intrapartum fever,

vi. Type of anaesthesia (local, regional, general),

vii. Experience of the operator (number of years experience in obstetrics),

viii. Centre or Country (numbers permitting).

Further exploratory analysis will be performed to generate hypotheses for future testing. This will include the effects of other interventions and techniques used during the operation and the effect these have on the outcomes.

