### Factorial design

Factorial trials maximise the efficiency of a trial by including more than one trial question into a single trial population. Instead of having one trial which compares, for example, single versus double layer closure of the uterine incision and another trial comparing closure versus non-closure of the peritoneum, both comparisons can be combined into one trial using only the number of women necessary to answer one of these questions in isolation.

In the CORONIS Trial five comparisons will be carried out in one trial, using a 2 × 2 × 2 × 2 × 2 factorial design. Such a design has rarely been used [24,25], but is appropriate for the evaluation of several procedures which will be used together in clinical practice. In this trial of different caesarean section techniques, using five pairs of possible allocated interventions (1 versus "not 1", 2 versus "not 2", 3 vs versus "not 3", 4 versus "not 4", 5 versus "not 5"), participants can receive one of 32 possible alternatives.

In the analysis of a factorial trial the same process is used for a 2 × 2 × 2 × 2 × 2 factorial design as for a 2 × 2 factorial design. All those allocated 1 are compared with all those allocated "not 1" regardless of what other interventions were allocated, provided that there is no interaction. This is best illustrated using an example. Consider a 2 × 2 factorial trial comparing the effects of single versus double layer closure of the uterine incision and closure versus non-closure of the peritoneum. Hence, there are four groups in the trial:

• single layer and closure of the peritoneum

• single layer and non-closure of the peritoneum

• double layer and closure of the peritoneum

• double layer and non-closure of the peritoneum

A simple example (Table 5) of no interaction being present. Here, the febrile morbidity risk ratio for double versus single layer uterine closure is the same in those who had closure of the peritoneum (20% vs 10% gives risk ratio = 2) and those who had non-closure (30% vs 15% gives risk ratio = 2). Therefore, the single layer and double layer groups may be combined and the analysis is based on the (bold) marginal totals (25% vs 12.5% gives risk ratio = 2).

**Table 5 T5:** Example of no interaction present

	**Single**	**Double**	**Total**
**Closure**	10/100 (10%)	20/100 (20%)	**30/200 (15%)**
**Non-closure**	15/100 (15%)	30/100 (30%)	**45/200 (22.5%)**
**Total**	**25/200 (12.5%)**	**50/200 (25%)**	**75/400 (18.75%)**

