## Sample size

In our pilot survey of 855 consecutive women undergoing caesarean section from 9 hospitals, the incidence of serious maternal morbidity before discharge from hospital was 11.6% (95% CI: 9.6–13.9). Inclusion of outcomes up to six weeks after the caesarean section is therefore likely to increase the incidence of the primary outcome to at least 15%. Assuming the incidence of the primary outcome is 15% in one group, then 7,586 women would need to be randomised to give 80% power to detect a risk ratio between the two groups of 0.85 (i.e. a reduction in incidence to 12.75%; (Table 7). A trial of this size will have in excess of 95% power to detect a risk ratio of 0.80 (e.g. to compare 15% with 12%).

**Table 7 T7:** Sample size

**Incidence in control group**	**Incidence in intervention group**	**Risk ratio**	**Total sample size needed for analysis of each comparison**
15%	18%	1.20	4,936
15%	17%	1.13	10,746
15%	13%	0.87	9,646
**15%**	**12.75%**	**0.85**	**7,586**
15%	12%	0.80	4,204
15%	11%	0.73	2,316

Sample sizes required for 15% incidence of primary outcome in control group, with 80% power

In order to ensure that there are 7,586 women included in the analysis of each comparison, a larger number of women need to be recruited. First, in order to carry out five comparisons when each centre takes part in only three, 12,668 women (7,586 × 1.67) would need to be recruited. Second, allowing for 15% loss to follow-up, about 14,904 women (12,668/0.85) would need to be recruited. Hence, the final target sample size is 15,000 women (Table 7).

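### Observed fit decides whether risk ratios or risk differences are presented, a choice the data cannot make at the planned effects; main-effect tests are essentially unaffected

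*Protocol article*

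**What the plan says.** The Analysis section of the protocol article sets the risk ratio as the default: "the risk ratio for each outcome will be estimated for each of the five surgical techniques". The paragraph on interactions says that "pairwise interactions between any two interventions will be tested for and the results will be stratified accordingly if interactions are found", and the next sentence, offered as an alternative, says that "if risk differences provide a better fit to the data than risk ratios, then these will be presented instead". It gives no criterion of fit, does not name the outcomes or comparisons covered, and does not require the risk ratio to be kept when the risk difference is shown. The same paragraph concedes: "It is recognised that the study has low power to detect interactions".

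Elsewhere the protocol works on the risk ratio. In the Factorial design section, Table 5 is the example of no interaction because "the febrile morbidity risk ratio for double versus single layer uterine closure is the same in those who had closure of the peritoneum" as in those who had non-closure; Table 6 is judged in the same way. The Sample size section states that "7,586 women would need to be randomised to give 80% power to detect a risk ratio between the two groups of 0.85".

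**The concern.** Fit can be judged only from outcomes by allocated group, so the scale would be chosen after the results are seen. The rule replaces one measure with the other; it does not supplement it. Five comparisons in one trial could therefore be reported on different scales, with intervals that take no account of the selection.

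Interaction also depends on scale. Effects that are constant as risk ratios are in general not constant as risk differences, and the reverse. Because the protocol stratifies results when an interaction is found, a change of scale can turn a pooled result into a stratified one or the other way round.

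Two questions follow. Can a trial of this size tell which scale fits better? How often would the choice alter a conclusion?

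**Working it through.** **1. The plan's own figure.** Inputs from the Sample size section: 15% versus 12.75% and 80% power. Assumed: two-sided 5% (inferred from the 95% interval in the Analysis section) and 1:1 allocation. With mean risk 0.13875 and difference d = 0.0225:

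n = [1.96·√(2 × 0.13875 × 0.86125) + 0.8416·√(0.15 × 0.85 + 0.1275 × 0.8725)]² / 0.0225² = 3,704.2 per arm.

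Continuity correction: n/4 × [1 + √(1 + 4/(n·d))]² = 3,792.6, rounded up to 3,793 per arm, or 7,586 in total. The stated figure is reproduced.

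**2. Dependence on scale, from Table 5.** Risk ratios are 20/10 = 2 and 30/15 = 2. Risk differences are 20 − 10 = 10 points and 30 − 15 = 15 points. The protocol's example of no interaction thus has a 5-point interaction on the other scale. Conversely, strata of 10% versus 20% and 20% versus 30% (an illustration) share a 10-point difference but have risk ratios of 2 and 1.5.

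**3. Women available for one pair of interventions.** Three of five interventions can be chosen in 10 ways, and a given pair is in 3 of them. Assuming balanced combinations and the planned 15% loss, 0.30 × 15,000 × 0.85 = 3,825 women are analysed, about 956 in each of four cells.

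**4. Separation of the scales at the planned effect.** With two true risk ratios of 0.85 from 15%, the cells are 15%, 12.75%, 12.75% and 10.84%. Under constant risk differences the last cell would be 15 − 2.25 − 2.25 = 10.50%.

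- Departure from additivity: 10.84 − 10.50 = 0.34 points.
- Standard error: √[Σ p(1 − p)/956] = √(0.4466/956) = 2.16 points.
- z = 0.16; power to tell the scales apart is 5.3%, against a 5% floor.

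**5. Which scale would fit better, if fit were compared routinely.** Better fit is taken as the smaller Wald interaction statistic (200,000 simulated trials per setting, 3,825 women, both interventions with the same effect).

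| Risk ratio, both | Risk ratio scale fits better when true | Risk difference scale fits better when true | Power to separate |
|---|---|---|---|
| 0.85 | 52.8% | 53.4% | 5.3% |
| 0.80 | 55.4% | 57.2% | 5.9% |
| 0.73 (largest effect in Table 7) | 60.6% | 65.2% | 8.4% |

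At 0.85 the wrong scale wins in 100 − 52.8 = 47.2% of trials when the risk ratio model is true. Comparing maximised likelihoods with log and identity links (1,500 trials) gives 47% at 0.85 and 44% at 0.80, with simulation error of about √(0.25/1,500) = 1.3 points. If only one of the two interventions has an effect, the choice is 50:50. Even if all 12,750 analysed women informed one pair, the right scale would win in only about 56% at 0.85.

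**6. How often the choice changes the interaction verdict.** With 956 per cell and 5% Wald tests, the two interaction statistics correlate at 0.99 at risk ratio 0.85. One is significant and the other not in 1.9% of trials per pair; in 0.8% a significant risk-ratio interaction disappears on the risk difference scale. Disagreement is 0.3% with no effects, 3.5% at 0.80 and about 7% at 0.73.

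**7. Main effects.** At 15% versus 12.75% with 3,793 per arm:

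- Risk difference: z = 0.0225/√[(0.1275 + 0.1112)/3,793] = 2.84.
- Log risk ratio: z = ln(0.15/0.1275)/√[(0.85/0.15 + 0.8725/0.1275)/3,793] = 2.83.

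**The case against.** The case for leaving the clause alone has four parts.

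- **The scales nearly coincide here.** If the data cannot tell them apart, they will usually give the same verdict on interaction. Step 6 confirms this. Table 5, with risks of 10% to 30% and a risk ratio of 2, shows the principle and not the likely size. This stands.
- **Main effects are safe.** A risk ratio of 1 and a risk difference of 0 are the same null hypothesis, and the test statistics are almost identical. A reader might infer that the rule lets the trial pick whichever scale makes a technique look effective, or that the primary estimand is left open. The document does not support that: population, outcome, comparison, intention-to-treat analysis and default measure are all stated. Only the summary scale can move.
- **The clause may be narrow.** It directly follows the sentence on stratifying, and can mean that risk differences are shown in place of stratified results only when a risk-ratio interaction is found. The 47% assumes routine comparison of fit, which the protocol does not state. This reading is fair. It makes the switch rarer, but still lets an observed interaction be removed by a change of scale once the results are known.
- **There is caution in the same section.** It focuses on main effects, admits low power and asks for careful interpretation of interactions. That helps with interaction tests, but does not settle which scale is reported.

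Fit might also be judged across strata of baseline risk, where separation is easier. Assuming two equal strata at 10% and 20%, a risk ratio of 0.85 and 7,586 women, power is still 16% and the right scale is chosen in 68% of trials. Very large effects would separate the scales: with two risk ratios of 0.5, power is 56% and the risk ratio scale is correctly chosen in 86%. Such effects lie outside the range in Table 7.

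**Conclusion.** The point holds in limited form. The protocol states a data-driven rule for the reported scale with no criterion, against its own use of the risk ratio for sample size and for defining interaction. An analysis plan that is not shown could add detail, but the sentence would still need correcting.

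Within the planning range the data cannot make the choice: it is close to a coin toss at risk ratio 0.85, and right in at most about two trials in three at 0.73. These figures assume 15% baseline risk, balanced combinations, 15% loss and, for the win rates, routine comparison of fit.

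The damage is mainly to consistency and pre-specification of the reported estimates. An interaction would be created or removed only occasionally: about 2% of trials per pair at 0.85, 3.5% at 0.80 and 7% at 0.73, accumulating over several pairs. Conclusions on whether a technique has an effect are essentially untouched. It should be changed, but it does not threaten the trial's validity.

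**What to change.** In the Analysis section, name the risk ratio as the primary measure for all five comparisons and as the scale for the interaction tests. Report the risk difference with its interval beside it for every comparison, whatever the fit. Delete the clause that lets risk differences replace risk ratios. If a risk-ratio interaction is found, the risk differences already in the table let readers see whether it persists on that scale.

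The cost is a change of wording and one extra column in the results tables. The sample size stays at 7,586 per comparison and 15,000 in total.
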